|  |  |  |  |  |  |  |  |  |  |  |  |  |
| **Adverse event collection** |  | x | x | x | x | x | x | x | x | x | x | x |
|  |  |  |  |  |  |  |  |  |  |  |  |  |
| **Patient-Reported Outcome** |  |  |  |  |  |  |  |  |  |  |  |  |
| Quality of Life assessment (FACT-C) | x |  |  | x | x | x | x | x | x |  | x | x |
|  |  |  |  |  |  |  |  |  |  |  |  |  |
| **Patient survival status** |  |  |  |  |  |  |  |  |  |  | x | x |
| **Disease status** |  |  |  |  |  |  |  |  |  |  | x | x |

* Biochemistry tests include: blood urea nitrogen, creatinine, electrolytes, SGPT, SGOT, GGT, alkaline phosphatase, and bilirubin.

** Urine or serum pregnancy test for women of childbearing potential and who are sexually active must be performed at baseline and at least every month during treatment.

¥ Free T4 and TSH must be performed at baseline and at least every 8 weeks during treatment and at end of treatment or 30 days post-treatment safety follow-up.

† PD-L1 expression on Tumor and Immune Infiltrating T cells & CD4+, CD8+ and CD3+ T cell infiltration are determined on baseline biopsy, D10 and surgical resection specimen.

‡ The microsatellite instability (MSI or MMR status) is determined once on either the baseline biopsy or D10 biopsy.

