### Clinical information

As of the date of avelumab’s IB (31 March 2017), there are no completed clinical trials to report. No clinical trial is conducted over avelumab in locally-advanced rectal adenocarcinoma. However, avelumab at a dose of 10 mg/kg once every 2 weeks has demonstrated meaningful clinical activity across various tumor types (lung cancer, ovarian cancer, gastric cancer, gastroesophageal junction cancer, urothelial carcinoma, mesothelioma, and adrenocortical carcinoma) and treatment settings. Across the aforementioned tumor types, responses with avelumab were typically observed early during treatment and appear durable in nature, including ongoing responses lasting > 1 year in several of the different cohorts. Overall, many responders were still experiencing ongoing response at the time of the data cutoff for the analysis.

As for safety data from subjects with different tumor types treated with avelumab, they suggest an acceptable safety profile of the compound. Most of the observed events were either in line with those expected in subjects with advanced solid tumors or with similar class effects of mAb blocking the PD-1/PD-L1 axis. Infusion-related reactions including drug hypersensitivity reactions and immune-mediated adverse reactions (immune-related pneumonitis, immune-related colitis, immune-related hepatitis, immune-related endocrinopathies (thyroid disorders, adrenal insufficiency, new onset type I diabetes mellitus, pituitary disorders), immune-related nephritis and renal dysfunction and other immune-related adverse events (AEs: myositis, myocarditis, Guillain-Barré syndrome, uveitis) have been identified as important risks for avelumab. The known and potential risks and benefits to the patient are further discussed in Section 9.2.

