| *Local guidelines, or e.g. ESC or AHA guidelines  ESC guidelines website: https://www.escardio.org/Guidelines/Clinical-Practice-Guidelines  AHA guidelines website: http://professional.heart.org/professional/GuidelinesStatements/searchresults.jsp?q=&y=&t=1001 | | | | | | | | |
| Endocrine irAEs | | | | | | | | |
| Endocrine Disorder | | Initial Management | | | | | Follow-up Management | |
| **Grade 1 or Grade 2 endocrinopathies (hypothyroidism, hyperthyroidism, adrenal insufficiency, type I diabetes mellitus)** | | Continue avelumab therapy.  Endocrinology consult if needed.  Start thyroid hormone replacement therapy (for hypothyroidism), anti‑thyroid treatment (for hyperthyroidism), corticosteroids (for adrenal insufficiency) or insulin (for Type I diabetes mellitus) as appropriate.  Rule-out secondary endocrinopathies (i.e. hypopituitarism / hypophysitis). | | | | | Continue hormone replacement/suppression and monitoring of endocrine function as appropriate. | |
| **Grade 3 or Grade 4 endocrinopathies (hypothyroidism, hyperthyroidism, adrenal insufficiency, type I diabetes mellitus)** | | Withhold avelumab therapy.  Consider hospitalization.  Endocrinology consult.  Start thyroid hormone replacement therapy (for hypothyroidism), anti‑thyroid treatment (for hyperthyroidism), corticosteroids (for adrenal insufficiency) or insulin (for type I diabetes mellitus) as appropriate.  Rule-out secondary endocrinopathies (i.e. hypopituitarism / hypophysitis). | | | | | Resume avelumab once symptoms and/or laboratory tests improve to Grade ≤ 1 (with or without hormone replacement/suppression).  Continue hormone replacement/suppression and monitoring of endocrine function as appropriate. | |

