      - - Will be quantified in mm2 in the most abundant tumor-infiltrating area in both, the stroma and the tumor, of the D10 biopsy (continuous variable).
        - After the recruitment of around 5 patients, a cut-off value will be agreed upon and the numerical values corresponding to T cell infiltration (continuous variable) will then be classified as low or high or not applicable (categorical variable).
    - Microsatellite instability (MSI or MMR status):
      - - Will be evaluated once on either the baseline biopsy or D10 biopsy.
        - The MSI predictive markers to be assessed are: MLH-1, MSH-2, MSH-6, and PMS-2.
    - Image of the biopsy is to be provided.
    1. Concomitant medications
    2. Adverse event collection

### 8.2.3. Treatment period: visits 8 to 13

The procedures to be done from week 3 ± 3 days to week 13 ± 3 days (visits 8 to 14), starting D15 are as follows:

- - 1. Physical examination/vital signs/weight
    2. Laboratory tests:
    - Hematology assessments: CBC
    - Blood chemistry: BUN, creatinine, electrolytes, SGPT, SGOT, GGT, alkaline phosphatase, bilirubin
    - Urine or serum pregnancy test for women of childbearing potential who are sexually active
    - Free T4 and TSH
    1. Concomitant medications including mFOLFOX-6 chemotherapy protocol and anti-emetics:
    - Oxaliplatin 85 mg/m2 in a 2-hour infusion
    - Leucovorin 400 mg/m2 over 2 hours
    - 48-hour infusion of fluorouracil 2,400 mg/m2
    1. IMP administration: avelumab 10 mg/kg first administration at D15, then every 2 weeks for 6 cycles
    2. Adverse event collection
    3. Patient-reported outcome: quality of life assessment using FACT-C questionnaire

### 8.2.4. End of treatment visit including study completion and premature withdrawal: visit 13

Besides the procedures to be done at week 13 ± 3 days, tumor markers (CEA and CA 19-9) should be assessed at the end of treatment. Also, at the time patients discontinue the study treatment, a visit should be scheduled as soon as possible, but no later than 14 days from the last day of study medication, at which time all of the assessments listed for the End of Treatment visit will be performed. An End of Treatment eCRF page should be completed, giving the date and reason for stopping the study treatment.

### 8.2.5. Surgery: visit 14

Depending on the patient’s condition and laboratory exams, the procedures to be done 2 to 3 weeks ± 3 days after the last cycle of chemotherapy plus avelumab are as follows:

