### 9.2.3. Benefit / risk balance

Avelumab has already received [orphan drug](https://en.wikipedia.org/wiki/Orphan_drug) designation by the European Medicines Agency for the treatment of gastric cancer in January 2017. The US Food and Drug Administration (FDA) approved it on 23 March 2017 for Merkel-cell carcinoma, an aggressive type of skin cancer, under the name Bavencio® (a trademark of Merck KGaA, Darmstadt, Germany).

The aim of the present study is to evaluate the rate of pCR rate following short-course radiation then mFOLFOX-6/avelumab. The expected benefits of the proposed therapeutic strategy are:

- - 1. The addition of avelumab to mFOLFOX-6 chemotherapy after short-course radiation will increase the pathologic complete response rate for locally-advanced rectal cancer amenable to surgery compared to historical controls.
    2. The addition of avelumab to mFOLFOX-6 chemotherapy after short-course radiation will increase the 3-year progression-free survival rate for locally-advanced rectal cancer amenable to surgery compared to historical controls.
    3. The addition of avelumab to mFOLFOX-6 chemotherapy after short-course radiation will be safe and well-tolerated.

This protocol will allow the evaluation of the therapeutic relevance of the proposed strategy by reliable and clinically approved endpoints.

Infusion-related reactions including drug hypersensitivity reaction and immune-mediated adverse reactions (immune-related pneumonitis, immune-related colitis, immune-related hepatitis, immune-related endocrinopathies [thyroid disorders, adrenal insufficiency, new onset type I diabetes mellitus, pituitary disorders], immune-related nephritis and renal dysfunction and other immune-related AEs (myositis, myocarditis, Guillain-Barré syndrome, uveitis) have been identified as important risks for avelumab. However, the hypothesis of an increased risk of AEs is not highly plausible in this context. Nevertheless, this protocol will assess the safety of avelumab.

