## Assessment of safety

Secondary safety endpoints are the frequency, severity, and attribution of adverse events related to avelumab in a neoadjuvant setting.

AEs and SAEs from all patients followed throughout the study will be recorded and reported, as described in Section 9.5, whether or not the AE was determined to be related to the administration of IMP.

Safety evaluation will include the monitoring of the following items:

- - 1. Clinical assessments

| **Clinical assessment** | **Time of assessment** |
| --- | --- |
| Routine monitoring of vital signs (heart rate, blood pressure, and body temperature) | At inclusion  Every 2 weeks± 3 days during chemotherapy  Every 3 months after surgery for 3 years |
| Weight |
| Physical examinations: total body examination (i.e., general appearance, skin, neck, including thyroid, eyes, ears, nose, throat, lungs, heart, abdomen, back, lymph nodes and extremities) and a clinical neurological examination |
| Pelvic MRI (rectal protocol) | At inclusion  Prior to surgery: pelvic MRI (rectal protocol), optional |
| CT or PET scan of the chest and the abdomen | At inclusion |

- - 1. Laboratory assessment:

| **Blood assessments** | **Time of assessment** |
| --- | --- |
| CBC, BUN, creatinine, electrolytes, SGPT, SGOT, GGT, alkaline phosphatase, bilirubin | Prior to study initiation  Start of chemotherapy  Then every two weeks ± 3 days  Then prior to surgery |
| Free T4 and TSH | At inclusion  At least every 8 weeks during treatment  At end of treatment or 30 days post-treatment safety follow-up |
| Virology | At inclusion |

- - 1. Urine or serum pregnancy test:
       - For women of childbearing potential and who are sexually active must be performed at baseline and least every month during treatment.
       - It should be negative when the patient is enrolled in the study.

Significant findings of any safety evaluation must be recorded either on the Relevant Medical History/Current Medical Conditions eCRF (if present before signing informed consent) or on the AEs eCRF (if newly occurring or worsening since signing informed consent).

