### Baseline safety variables

All safety variables will be presented. Baseline data are defined as the last available data before the start of IMP infusion.

All laboratory data except those defined as efficacy variables (in the above section) or as exploratory variables will be defined as safety criteria. All laboratory data will not be displayed in the baseline section but in the analysis of safety in order to display in the same table the baseline and other data.

In addition, the frequency, grade, and attribution of surgical complications to the neoadjuvant treatment will be described using the Clavien-Dindo classification (to grade surgical complications).

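### New-onset type I diabetes is a named important risk of avelumab with graded management rules, yet none of the eight scheduled chemistry draws includes glucose

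*Protocol*

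**What the plan says.** Sections 1.3.2 and 9.2.3 list the immune-related endocrinopathies of avelumab as "thyroid disorders, adrenal insufficiency, new onset type I diabetes mellitus, pituitary disorders". Section 9.2.3 says that these and the other listed reactions "have been identified as important risks for avelumab".

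Table 3 (Section 6.4.2, endocrine events) puts type I diabetes in the same rows as hypothyroidism, hyperthyroidism and adrenal insufficiency. At Grade 1 or 2 avelumab continues and treatment is started: "corticosteroids (for adrenal insufficiency) or insulin (for Type I diabetes mellitus) as appropriate". At Grade 3 or 4 avelumab is withheld, and it resumes once symptoms and/or laboratory tests are back to Grade 1 or lower.

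The chemistry panel is itemised in the Table 1 footnote: "Biochemistry tests include: blood urea nitrogen, creatinine, electrolytes, SGPT, SGOT, GGT, alkaline phosphatase, and bilirubin". Section 8.2.3, for the avelumab visits, has the same content: "Blood chemistry: BUN, creatinine, electrolytes, SGPT, SGOT, GGT, alkaline phosphatase, bilirubin". Sections 8.2.1, 8.2.5, 8.3.1 and 10.2 repeat it. No HbA1c or urinalysis is scheduled either.

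Two recording rules matter here. Section 10.2 sends each significant safety finding to one of two eCRF pages, according to whether it was present before consent or is new or worse since. Section 12.6.4 adds: "Baseline data are defined as the last available data before the start of IMP infusion".

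**The concern.** Most laboratory-detectable toxicities in Table 3 have a scheduled test: transaminases and bilirubin for the liver, creatinine for the kidney, free T4 and TSH for the thyroid. Type I diabetes shares its Table 3 rows with the thyroid disorders, and its basic test is a routine analyte on a tube already being drawn, but it has none. Followed exactly as written, the protocol finds hyperglycaemia only when symptoms appear or when a site happens to test.

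Three things are at stake:

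- **Patient safety.** Insulin could be started late, and patients come to total mesorectal excision without a trial-required glucose value.
- **The adverse-event secondary endpoint.** It covers frequency, severity and attribution. With three sites and local laboratories, asymptomatic hyperglycaemia would be captured according to site habit. Table 3 also prescribes prednisone 1.0 to 2.0 mg/kg/day for several immune reactions, which is a second cause of high glucose. Separating the two is harder without serial values.
- **The reference value.** Medical history identifies known diabetes. For undiagnosed hyperglycaemia there is no scheduled value from which to decide whether a later finding is old or new.

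**Working it through.** The protocol states no figure on this point, so there is nothing to reproduce. The check is a count of what is scheduled, followed by an illustrative probability.

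**1. Required analytes by list**

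| Place in protocol | Applies to | Glucose listed |
| --- | --- | --- |
| Table 1 footnote | all chemistry draws | no |
| Section 8.2.1 | visit 1 | no |
| Section 8.2.3 | visits 8 to 13 | no |
| Section 8.2.5 | visit 14 | no |
| Section 8.3.1 | laboratory table | no |
| Section 10.2 | safety laboratory table | no |

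The verb in the footnote could be read as open-ended. The five other lists have the same content, however, so nothing in the protocol obliges a site to measure glucose.

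**2. Number of draws.** Table 1 marks biochemistry at visit 1, visits 8 to 13 and visit 14.

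- Per patient: 1 + 6 + 1 = 8.
- In the planned 44 patients: 8 × 44 = 352.
- Draws that require glucose: 0 of 8 per patient, 0 of 352 overall.

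**3. Length of the gap.** The first avelumab dose is in week 3 and surgery in week 16 or 17: 16 − 3 = 13 weeks to 17 − 3 = 14 weeks.

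**4. Chance that the gap matters for type I diabetes.** Two inputs are not in the text and are assumed: an incidence *r* of 0.1% to 1%, and a share *s* of 10% to 50% of cases that only a scheduled test would reveal. With *n* patients:

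- P(at least one case) = 1 − (1 − *r*)^*n*
- P(at least one case seen only by a scheduled test) = 1 − (1 − *r s*)^*n*

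For *n* = 44:

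- Any case: 1 − 0.999^44 = 0.043; 1 − 0.99^44 = 0.357.
- Seen only by a scheduled test: 1 − (1 − 0.001 × 0.10)^44 = 0.004; 1 − (1 − 0.01 × 0.50)^44 = 0.198.

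The planned 44 is an upper limit. With the 36 patients of the primary analysis, the second range is 1 − 0.9999^36 = 0.004 to 1 − 0.995^36 = 0.165. If the trial stops after 13 patients, it is 1 − 0.9999^13 = 0.001 to 1 − 0.995^13 = 0.063. Steroid-related hyperglycaemia is not counted in any of these figures.

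**5. Baseline.** Section 12.6.4 takes the last value before the first infusion, and no scheduled draw supplies a glucose value. The visit 1 draw follows consent but precedes radiotherapy and avelumab, so a glucose result from it would serve as the pre-treatment reference.

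**The case against.** The strongest reply is that nothing is contradicted. The protocol never promises scheduled glucose. Table 3 says what to do once an event is recognised, and its restart rule accepts symptoms or laboratory tests, so it works with unscheduled testing. Sections 10.2 and 12.6.4 govern data that exist and do not require every analyte to be scheduled. This is right: the finding is a gap in the schedule and breaks no rule.

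Second, adrenal and pituitary disorders are in the same list of important risks and have no scheduled cortisol or ACTH, so singling out glucose may look selective. The distinction that holds is practical. Glucose is one routine analyte that fits the existing panel, whereas those work-ups need additional tests. Leaving them clinically triggered, as the cardiac work-up is, is defensible.

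Third, other safeguards exist: vital signs, weight and physical examination at each avelumab visit, open questioning about health, adverse-event collection throughout, and safety follow-up to 90 days after the last dose. Clinically significant laboratory abnormalities count as adverse events, and sites may well test glucose anyway. These help with symptomatic disease. They do not find asymptomatic hyperglycaemia, and they do not make testing uniform across sites.

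Fourth, the probability range is wide and rests on assumed inputs, and its upper end needs both at their maximum. That stands, and the range should be read as illustrative. The case for the change does not depend on it.

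**Conclusion.** The concern holds. An important risk with graded management rules has no scheduled test at baseline, at any of the six avelumab doses or before surgery, although the comparable liver, renal and thyroid toxicities do. The count of 0 of 8 draws per patient comes straight from the protocol and needs no assumption. The 0.4% to 20% chance of at least one case in 44 patients that only a scheduled test would reveal (4% to 36% for any case) depends on the assumed incidence and share, and it is lower if fewer patients are treated.

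The consequence is limited. The pCR analysis is untouched, Grade 1 or 2 diabetes does not change avelumab dosing, and the event is rare. The change should still be made, because it improves safety monitoring and the consistency of the adverse-event endpoint at very small cost, and values that were never measured cannot be recovered at the analysis stage.

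**What to change.** Add glucose to the biochemistry panel in all six places where it is itemised (the Table 1 footnote and Sections 8.2.1, 8.2.3, 8.2.5, 8.3.1 and 10.2), measured at the 8 draws already scheduled. Leave Table 3 unchanged, and leave adrenal, pituitary and cardiac work-up clinically triggered.

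The cost is one inexpensive analyte on blood already taken (up to 352 results), one eCRF field and one short amendment covering the six lists. There is no new visit or procedure. Some incidental or steroid-related high values will need follow-up.

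The amendment should also settle who pays. Section 17 (Indemnity) treats pre-treatment biochemistry as standard of care paid by the patient, and thyroid tests as trial-specific. Listing glucose with the thyroid tests is the simple solution, which means one further entry in Section 17.

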# INTRODUCTION AND BACKGROUND INFORMATION

## Disease and context

Colorectal cancers are among the most common cancers worldwide, and there is a high mortality rate for advanced-stage disease. The incidence and mortality rates have been steadily declining over the past two decades, largely through advances in screening and improvements in treatment. However, rectal cancer remains a significant cause of morbidity and mortality worldwide (Kothari N et al., 2015). The significant majority of rectal cancers are carcinomas, which are primarily comprised of adenocarcinomas. For the best outcome, these cancers require a multidisciplinary approach including chemotherapy, radiation, and surgery (Kothari N et al., 2015).

Patients with locally-advanced rectal cancer are treated with neoadjuvant chemoradiation before total mesorectal excision (TME) to induce tumor regression, increase the probability of achieving resection with negative margins, and reduce the risk of local recurrence. Post-operative adjuvant chemotherapy is also recommended in these patients to reduce the risk of distant metastasis. This multimodality treatment achieves high levels of local tumor control and good long-term survival (Sauer R et al., 2004). However, TME is associated with some mortality, morbidity, and long-term sequelae that have a substantial negative effect on quality of life (Williams NS et al., 1983).

Also and despite the use of peri-operative radiation and chemotherapy, outcomes for patients with locally-advanced rectal adenocarcinoma remain poor with 3-year disease-free survival (DFS) approximately 50% (Bujko K et al., 2016a; Nilsson et al., 2013). The use of single-agent immune checkpoint inhibitors in microsatellite-stable colorectal cancer has shown limited efficacy. However, the strategy of combining immune checkpoint inhibition with systemic chemotherapy after radiation is a novel approach that has the potential to overcome these limitations.

## Target

Avelumab, (company code: MSB0010718C) the investigational medicinal product (IMP), is a fully human antibody (calculated molecular weight of 143,832 Dalton) of the immunoglobulin G 1 (IgG1) isotype. It specifically targets and binds the programmed death ligand-1 (PD-L1), the ligand for PD-1, and blocks the interaction between PD-L1 and PD-1. This removes the suppressive effects of PD-L1 on anti-tumor CD8+ T cells, resulting in the restoration of cytotoxic T cell response. Monoclonal antibodies targeting PD-1 and PD-L1 have shown antitumor activity in a range of human solid tumors, including melanoma and cancers of the lung, kidney, head and neck, bladder, stomach, and breast (Chen I et al., 2015).

Avelumab has received [orphan drug](https://en.wikipedia.org/wiki/Orphan_drug) designation by the European Medicines Agency for the treatment of [gastric cancer](https://en.wikipedia.org/wiki/Gastric_cancer) in January 2017. The US Food and Drug Administration (FDA) approved it on 23 March 2017 for [Merkel-cell carcinoma](https://en.wikipedia.org/wiki/Merkel-cell_carcinoma), an aggressive type of skin cancer, under the name Bavencio® (a trademark of Merck KGaA, Darmstadt, Germany). Although other agents targeting PD-L1 are in clinical development, to the best of our knowledge, avelumab is the first human anti-PD-L1 IgG1 antibody with a native Fc region. This means it is capable of inducing antibody-dependent cell-mediated cytotoxicity (ADCC) against PD-L1+ tumor cells *in vitro* and elimination of ADCC potential *in vivo* significantly reduced anti-tumor activity (Boyerinas B, 2015).

